### Randomisation

We used the MRC computerised telephone randomisation service in Aberdeen, which provides an efficient automated 24-hour service and the choice of randomisation by telephone or Internet in each case. Randomisation was at the patient level within each practice, using a block design to maintain a balance of numbers in the control and intervention groups.

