### Proposed sample size

We conducted two sample size calculations - for both a 4 and 5 point difference in the primary outcome measure, the BDI-II. In order to detect a 4-point difference on the BDI-II (assuming a pooled standard deviation of 11.0) at 90% power and the 5% level of significance, the required sample size was 318. To meet the objectives of the economic analysis (see details below) data from a previous trial comparing GP care and talking therapies showed a sample size of approximately 200 in each study arm would be required, rising to 534 using an estimated 25% drop-out rate [30].

To take account of practice clustering we used an intra-class correlation (ICC) of 0.02 which, given an estimated 12 to 14 patients recruited per practice, inflated our sample size to 630 from 47 practices (see table 2 below). We considered this to be a suitable ICC given that a primary care trial with the BDI as the outcome for GPs using cognitive behavioural techniques with their patients gave an ICC of 0.13 [31].

**Table 2 T2:** Four Point Difference in BDI

ICC	Design effect*	Total sample size		Number of practices required
		Required	With 25% drop-out	
0	1	400	534	40
0.01	1.09	436	581	44
**0.02**	**1.18**	**472**	**630**	**47**
0.03	1.27	508	678	51
0.04	1.36	544	725	54
0.05	1.45	580	774	58

*Design effect = 1 + (n-1) × ICC, based on clusters with 10 individuals per cluster.

A 4 point difference in BDI score would be a conservative result and is the smallest difference we would expect to achieve. In a previous trial of counselling in primary care the results showed a 5 point difference in outcome which is equivalent to a clinically important treatment effect of 0.5 [31].

We therefore repeated the same calculations for a difference in outcome of 5 points on the BDI, which indicated that we would need 423 participants from as few as 32 practices recruiting 12 to 14 patients each. This would also provide sufficient power for a cost-effectiveness analysis using this outcome.

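### The 5-point requirement of 423 participants from 32 practices does not follow from the stated inputs, and Table 2 is headed as a 4-point BDI calculation but is built on the economic figure of 400

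*Protocol article*

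**What the plan says.** All the figures are in the Protocol article, section Proposed sample size, including Table 2.

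- **BDI-II, 4 points.** "In order to detect a 4-point difference on the BDI-II", "assuming a pooled standard deviation of 11.0", and "at 90% power and the 5% level of significance, the required sample size was 318".
- **Economic analysis.** Data from a previous trial "showed a sample size of approximately 200 in each study arm would be required". That is 400 in total, which the article raises to 534 for 25% drop-out.
- **Clustering.** With an ICC of 0.02 and 12 to 14 patients recruited per practice, the total becomes 630 from 47 practices. The article refers to Table 2 for this.
- **Table 2** is headed "Four Point Difference in BDI". Its ICC 0 row reads 400 required, 534 with drop-out, 40 practices. Its footnote bases the design effect on 10 individuals per cluster.
- **BDI, 5 points.** The article says it repeated the same calculations, "which indicated that we would need 423 participants from as few as 32 practices recruiting 12 to 14 patients each". It adds: "This would also provide sufficient power for a cost-effectiveness analysis using this outcome".

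**The concern.** If only the target difference changes from 4 to 5 points, the sample size should fall by the factor (4/5)² = 0.64 and nothing else should move. Neither candidate 4-point total leads to 423 in this way: 630 × 0.64 = 403, and 501 (the total that follows from 318) × 0.64 = 321.

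Table 2 adds to the difficulty. Its heading names the 4-point BDI difference, yet the 318 just derived for that difference appears nowhere in it.

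The trial recruited 558, fewer than 630, and the Discussion says the numbers recruited should be enough to show a clinically significant effect. A reader judging that statement has to know what 630 and 423 are sized for. Read as headed, Table 2 says the 4-point BDI target was missed. On the stated inputs it was met.

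**Working it through.** **Inputs.** SD 11.0, 90% power, 5% significance, ICC 0.02, 25% drop-out and 10 per cluster are all from Proposed sample size and Table 2. Equal allocation is taken from the Randomisation section ("using a block design to maintain a balance of numbers in the control and intervention groups"). The article does not say one- or two-sided; I assume two-sided, and this reproduces its figure.

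**Formulas.** n per arm = 2 × (1.960 + 1.282)² × SD² / d². Design effect = 1 + (m − 1) × ICC. Recruited = required / (1 − 0.25).

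**Step 1: the article's own 4-point figure.** 2 × 10.51 × 121 / 16 = 158.9, so 159 per arm and 318 in total. This matches.

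**Step 2: Table 2.** The design effect at ICC 0.02 is 1 + 9 × 0.02 = 1.18. 400 × 1.18 = 472; 472 / 0.75 = 629.3 (printed 630); 472 / 10 = 47 practices. The other rows follow from 400 in the same way (for example 400 × 1.45 = 580 at ICC 0.05), so the base is 400 throughout.

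From 318 the ICC 0.02 row would be 318 × 1.18 = 375.2 (376), then 375.2 / 0.75 = 500.3 (501), from about 38 practices (376 / 10).

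**Step 3: 5 points, all else unchanged.** 2 × 10.51 × 121 / 25 = 101.7, so 102 per arm and 204 in total. 204 × 1.18 = 240.7 (241); 240.7 / 0.75 = 321 recruited; 241 / 10 = about 24 practices.

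**Step 4: sensitivity to cluster size.**

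| m | Design effect | Completers | Recruited | 423 is higher by |
|---|---|---|---|---|
| 10 | 1.18 | 240.7 | 321 | 32% |
| 12 | 1.22 | 248.9 | 332 | 27% |
| 14 | 1.26 | 257.0 | 343 | 23% |

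The 10 and the 12 to 14 can be reconciled: 12 to 14 recruited less 25% leaves 9 to 10.5 analysed per practice. The choice of cluster size does not explain 423.

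**Step 5: what would give 423.** Starting from 204, the design effect would have to be 423 × 0.75 / 204 = 1.555, an ICC of 0.555 / 9 = 0.062 with 10 per cluster (0.043 with 14). With the design effect kept at 1.18, the SD would have to be about 12.6. Using the standardised effect of 0.5 that the article quotes for 5 points moves the other way: 170 × 1.18 / 0.75 = 268.

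Four routes land on or near 423, and each changes a stated input:

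- 400 × 0.64 = 256; × 1.24 (13 per cluster) = 317.4; / 0.75 = 423.3; and 317.4 / 10 = 32 practices.
- 318 / 0.75 = 424, and 318 / 10 = 32 practices. This is the 4-point figure without clustering.
- 95% power with 14 per cluster: 252 × 1.26 / 0.75 = 423.4.
- ICC 0.05 with 12 per cluster: 204 × 1.55 / 0.75 = 421.6.

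**Step 6: the cost-effectiveness sentence.** 423 × 0.75 = 317 completers. The section gives about 400 for the economic analysis (472 after clustering); 317 / 400 = 79%.

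**Step 7: power for the BDI.** 558 × 0.75 / 1.18 = 354.7 effective, or 177.3 per arm. The standard error is 11 × √(2 / 177.3) = 1.168; 4 / 1.168 − 1.96 = 1.46, which is about 93% power for 4 points. At the 67% response reported for 12 months, 558 × 0.67 / 1.18 = 317 effective, about 90%. For 423 recruited and 5 points, 317.25 / 1.18 = 268.9 effective, about 96%.

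**The case against.** Four arguments can be made for the article.

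**423 has a sensible source.** Rescaling 400 by 16/25 with 13 per cluster reproduces both 423 and 32 practices, and 13 lies within the stated 12 to 14. It fits better than 318 / 0.75, which is 424. So a reader who infers that 423 is simply the unclustered 4-point figure printed in the wrong place goes beyond the document. Neither route can be confirmed. The better-fitting one still scales an economic requirement as if it were a BDI calculation, and it uses a different cluster size from Table 2; with Table 2's 1.18 it gives 403. The mismatch with the stated inputs therefore stands.

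**630 is legitimate.** The text introduces 400 and 534 as the economic requirement just before inflating to 630, and sizing a trial on the larger of two requirements is normal practice. This stands: 630 is traceable and is not an arithmetic error. What remains is that the table's heading assigns it to the wrong requirement.

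**The economic requirement may differ at 5 points.** The sentence refers to a cost-effectiveness analysis using this outcome, and the Economic Analysis section links costs to BDI-II change. A larger assumed effect could therefore need fewer participants. A reader might infer from 317 against 400 that the claim is false. The article does not establish that, because it never says the 400 applies at both differences, and the source of the 200 per arm is not shown. The claim is unsupported rather than disproved.

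**Nothing was harmed.** Both discrepancies are on the conservative side for the BDI comparison. This stands, and it limits how serious the point is.

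**Conclusion.** The point holds as a fault in the stated sample size justification.

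- The 5-point figure does not follow from the article's inputs: 423 printed against about 321 (332 to 343 with 12 to 14 per cluster). This assumes a two-sided test, equal arms and the normal approximation, which together reproduce the article's 318.
- Table 2's heading does not match its content. At ICC 0.02 a 4-point BDI row would be about 376 and 501, against 472 and 630 printed.
- The cost-effectiveness sentence has no calculation behind it and sits uneasily with the roughly 400 given earlier in the section.

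It would be wrong to conclude that the trial is too small for its primary outcome. The 558 recruited exceed the re-derived 4-point need of about 501. The economic position is less comfortable than the 423 sentence suggests: 558 × 0.75 = about 418 completers, above 400 but below 472. This assumes 25% loss of economic data.

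**What to change.** Correct the text and Table 2; recruitment is unaffected.

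1. Use one cluster size throughout, and say whether it counts patients recruited or patients analysed.
2. Restate the requirements as three labelled lines. With 10 per cluster, ICC 0.02 and 25% drop-out, as base, after clustering, recruited:
   - 4-point BDI: 318, 376, about 501
   - 5-point BDI: 204, 241, about 321
   - economic: 400, 472, 630

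   If 423 came from other inputs, print them instead.
3. Relabel Table 2 so that its base is shown as the economic 400.
4. Give the basis for saying that the 5-point size suffices for cost-effectiveness, or delete the sentence.

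The cost is a few lines of text and a table heading.

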### Planned analyses

All data will be double entered, using a reputable data entering service, blind as to participant group.

A description of baseline characteristics will be made between those randomised to the control and intervention groups.

All outcome analyses will include individuals in their randomised arm (intention to treat). Initial descriptive statistics will be used to summarise the differences in outcome between the two groups. We will present means and standard deviations for normally distributed, continuous variables and medians, with inter-quartile ranges, for those not normally distributed. Categorical outcomes will be presented as frequencies and percentages within each of the categories.

Observations at each time point on the same individual will not be independent so a repeated measures generalised linear model approach will be used [32]. This will also allow adjustments to be made for the natural clustering inherent in the study design. Continuous outcomes, which are measured at baseline and at the end of follow-up, will be analysed using analysis of covariance (ANCOVA) to adjust for any differences in baseline values [33]. Results will be presented as adjusted differences in means with 95% confidence intervals and associated p-values. Categorical outcomes will be compared using logistic regression and summarised by comparing the group values of the odds ratios for each outcome using 95% confidence intervals and associated p-values. Statistical techniques will be used to assess the impact of potential missing data [34]. Multiple imputation using a predictive model based approach will be used to impute missing values [35]. No interim or sub-group analyses are planned.

The impact of clustering by GP and/or nurse will be investigated using multi-level modelling. This will ensure that estimated standard errors of the treatment effect will be adjusted for the cluster effects.

### Economic Analysis

The economic evaluation will be conducted from two perspectives: (i) focusing on service costs (public expenditure) and (ii) a societal perspective including service costs, productivity losses and informal care inputs. Service costs will be calculated by attaching unit costs to data reported on the CSRI using, wherever possible, national unit costs from publicly-available sources or estimated using an equivalent approach [36,37]. The service use patterns and associated costs for the two groups will be compared at each time point and changes over time will be analysed using standard non-parametric techniques.

Cost-effectiveness will be assessed using the net-benefit statistic, a reformulation of the cost-effectiveness decision rule that does not rely on cost-effectiveness ratios with their associated statistical problems [38]. This will allow the cost-effectiveness analysis to be formulated within a standard regression type framework [39]. Inclusion of the EQ-5 D allows a cost-utility analysis and a cost-effectiveness analysis will link total costs with the primary clinical outcome measure (change in the level of depression using the Beck Depression Inventory-II) and the number of depression-free days (see above). A cost-consequence analysis will explore the relationship between cost, characteristics, needs and outcome measures [40]. All analyses will take into account cluster effects in practices and sensitivity analyses will check assumptions made in the cost calculations and analyses.

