**Methods/Design:**

Participants were recruited from 42 general practices throughout the United Kingdom. Eligible participants had to have a history of chronic major depression, recurrent major depression or chronic dsythymia confirmed using the Composite International Diagnostic Interview (CIDI). They also needed to score 14 or above on the Beck Depression Inventory (BDI-II) at recruitment.

Once consented, participants were randomised to treatment as usual from their general practice (controls) or the practice nurse led intervention. The intervention includes a specially prepared education booklet and a comprehensive baseline assessment of participants' mood and any associated physical and psycho-social factors, followed by regular 3 monthly reviews by the nurse over the 2 year study period. At these appointments intervention participants' mood will be reviewed, together with their current pharmacological and psychological treatments and any relevant social factors, with the nurse suggesting possible amendments according to evidence based guidelines. This is a chronic disease management model, similar to that used for other long-term conditions in primary care.

The primary outcome is the BDI-II, measured at baseline and 6 monthly by self-complete postal questionnaire. Secondary outcomes collected by self-complete questionnaire at baseline and 2 years include social functioning, quality of life and data for the economic analyses. Health service data will be collected from GP notes for the 24 months before recruitment and the 24 months of the study.

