### Secondary outcomes (table 1)

**Table 1 T1:** Frequency of measuring outcome measures

	BDI-II	WASAS	CIDI (24 months)	SAPAS	EQ-5D	CSRI	Service Data (24 months)
**Baseline**	√	√	√	√	√	√	√
**3 months***	√						
**6 months**	√						
**12 months**	√						
**18 months**	√						
**24 months**	√	√	√		√	√	√

* We had initially planned to collect BDI-II questionnaires 3 monthly, but decided this was too onerous for participants and risked a poor response rate, so this was altered to 6 monthly from the 6 months time-point

(a) Depression-Free Days: These will be assessed in two ways. They will be calculated using BDI-II assessment scores following the method of Lave et al. [25]. This will then be compared with patients' self-completed records of which days they felt they were significantly depressed, to see how a continuous form of data collection compares with a statistical method for assessing persistence of depression. (Our feasibility data indicates that patients will be prepared to keep such on-going records).

(b) Social Functioning: This will be measured using the Work and Social Activity Scale (WASAS). This is a well-established, brief questionnaire, which we will use to assess participants' difficulties with physical and social functioning associated with their depression [26]. It has been validated for use in primary care populations with depression.

(c) Frequency of Depressive Episodes: Will be collected using the CIDI questionnaire [20]. This instrument is frequently used in psychiatric epidemiological studies and has been modified to allow us to collect diagnostic data on trial participants as regards their depression using DSM-IV criteria for the 36 months before recruitment as well as the 24 months of the trial.

(d) Patient personality factors: Participants are asked at baseline to complete the Standardised Assessment of Personality - Abbreviated Scale (SAPAS), a brief measure of personality variables developed for use in primary care [27].

(e) Quality of life: This will be measured by the Euroquol EQ-5 D, which will generate scores for the cost-utility analysis [28].

(f) Resource use and costs: Data on all services used and productivity losses over a retrospective 3-month period will be collected using a modified version of the Client Service Receipt Inventory (CSRI), which has been used in numerous economic evaluations, including in primary care populations [29].

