(g) Practice service data: The research nurses will also be asked to count the number of GP attendances and home visits, practice nurse contacts, referrals for psychological therapy and prescriptions for psychotropic medication for all participants for the 24 months before recruitment and the 24 months of the trial.

In order to maintain blindness the final research assessment will be carried out by a different person. This may be another nurse at the practice, a MRC GPRF regional training nurse or a Mental Health Research Network Clinical Studies Officer. All participants will be asked at the outset of the final assessment not to reveal their trial arm allocation. As a check on potential bias, each practitioner assessing outcome will be asked to record which trial arm they think each patient they have assessed was in, to see whether the probability of a correct 'guess' is greater than chance.

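### The between-arm comparison of service use and costs is set out by time point and by change, with no baseline adjustment stated, although the protocol's rule for outcomes measured at baseline and 24 months is ANCOVA

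*Protocol article*

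**What the plan says.** Resource use and costs are secondary outcome (f) in the protocol article: "Data on all services used and productivity losses over a retrospective 3-month period will be collected", by means of an adapted Client Service Receipt Inventory (CSRI). Table 1 ticks the CSRI at baseline and at 24 months only. The abstract agrees: "Secondary outcomes collected by self-complete questionnaire at baseline and 2 years include social functioning, quality of life and data for the economic analyses".

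Two sections then say how such data are to be analysed.

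- Planned analyses: "Continuous outcomes, which are measured at baseline and at the end of follow-up, will be analysed using analysis of covariance (ANCOVA"), with results reported as adjusted differences in means. No exception is made for costs.
- Economic Analysis, on service use and what it costs: "costs for the two groups will be compared at each time point and changes over time will be analysed", by standard non-parametric methods. No baseline covariate is mentioned.

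Economic Analysis also plans a net-benefit analysis, of which it says: "This will allow the cost-effectiveness analysis to be formulated within a standard regression type framework". It adds that all analyses will allow for practice clustering.

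**The concern.** With two measurement times, the phrase about each time point can only mean baseline and 24 months, and the phrase about changes over time can only mean the change between them. As written, the 24-month comparison makes no use of the participant's own earlier cost. The change analysis subtracts that cost in full, which over-corrects unless the two measurements are very highly correlated. A model with baseline as covariate lies between these extremes and is at least as precise as either.

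Two things are at stake. The first is precision in a noisy, skewed outcome. The second is clarity: when baseline costs differ by chance, the 24-month and change comparisons can point different ways. The section does not say which is the main one, and neither matches the rule given for other outcomes on the same schedule.

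**Working it through.** **Do the two rules meet on the same data?** Cost is continuous, is listed as a secondary outcome, and is measured at baseline and at the end of follow-up. That is the class to which Planned analyses assigns ANCOVA. Economic Analysis attaches unit costs to the CSRI, so its comparison concerns the same data. Practice service counts are also paired ("for all participants for the 24 months before recruitment and the 24 months of the trial"), but the costs are built on the CSRI and the point is confined to it.

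**The plan's own economic figure.** Proposed sample size gives about 200 per arm, raised to 534 for 25% drop-out: 400 / (1 − 0.25) = 533.3, rounded up to 534. This reproduces. The documents give no figure for the precision of the cost comparison.

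**Precision.** Let σ² be the variance of cost, assumed equal at both times, and ρ the baseline-to-24-month correlation. The documents give no ρ, so a range is assumed. The variance of the between-arm difference is proportional to:

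- 24 months only: σ²
- change: 2σ²(1 − ρ)
- baseline-adjusted: σ²(1 − ρ²)

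Relative to baseline adjustment, change has 2(1 − ρ)/(1 − ρ²) = 2/(1 + ρ), and 24 months only has 1/(1 − ρ²).

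| Assumed ρ | Change: 2/(1 + ρ) | 24 months only: 1/(1 − ρ²) |
|---|---|---|
| 0.2 | 2/1.2 = 1.67 | 1/0.96 = 1.04 |
| 0.3 | 2/1.3 = 1.54 | 1/0.91 = 1.10 |
| 0.5 | 2/1.5 = 1.33 | 1/0.75 = 1.33 |
| 0.7 | 2/1.7 = 1.18 | 1/0.51 = 1.96 |

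Both ratios exceed 1 for every ρ between 0 and 1. Below 0.5, change is noisier than ignoring baseline; above 0.5 the order reverses. No value of ρ makes both comparisons efficient.

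**Does skewness alter this?** Lognormal costs were simulated with log SD 1, 200 per arm and 4,000 replicates. The SDs of the estimated mean difference for 24 months only / change / adjusted were:

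- raw correlation about 0.21: 0.216 / 0.269 / 0.211
- about 0.39: 0.216 / 0.239 / 0.198
- about 0.60: 0.216 / 0.198 / 0.173

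Squared ratios follow the formulas closely. At 0.39, for example, change to adjusted is (0.239/0.198)² = 1.46, against 2/1.39 = 1.44.

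**Do rank methods alter this?** A rank-only simulation assumed lognormal costs with log SD 1, a cost ratio of 1.25 and 187 per arm. None of these is taken from the documents as a CSRI figure. Approximate power was:

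| Log-scale correlation | Rank test on change | Rank test at 24 months | Rank ANCOVA |
|---|---|---|---|
| 0.3 | 40% | 56% | 59% |
| 0.5 | 52% | 56% | 67% |
| 0.7 | 72% | 56% | 82% |

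Repeat runs agreed to within about three percentage points. The ordering is the same as for means, so a non-parametric method does not by itself remove the loss.

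**The case against.** The strongest reply is that Economic Analysis is a specific rule for economic data, and a specific rule normally overrides a general one. It also covers service use patterns, some of which need not be continuous. Part of this stands: ANCOVA does not clearly reach every service-use item. For cost itself, however, the article does not say that the general rule is displaced. If it is displaced, what remains is still the less precise choice.

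A second reply is that the text never says the comparisons are unadjusted. A bootstrapped regression with baseline cost as covariate would satisfy both sections. This is correct, and it is why the point is that adjustment is not stated, not that it is ruled out.

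A reader might go further in four ways that the documents do not support.

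- *The cost-effectiveness conclusion is undermined.* That conclusion runs through the net-benefit regression. The covariates of that model are detail that an article commonly leaves to the fuller plan, so their absence is not a finding.
- *The plan tests baseline costs for differences.* The text says only that the groups are compared, and a description by arm may be all that is meant.
- *The loss equals a definite number of participants.* That would need the 24-month CSRI response, which is not given. The 67% in Use of Vouchers is the 12-month return of a postal BDI-II, whereas the 24-month questionnaires are handed out in a booklet at the surgery.
- *Both comparisons lose heavily.* At ρ of 0.2 to 0.3 the 24-month comparison loses only about 4% to 10% in variance. The large loss belongs to the change analysis, which is planned beside it and not in its place.

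**Conclusion.** The point holds as an improvement to a secondary economic comparison. Cost is governed by two rules, and the one in Economic Analysis, as stated, does not use the baseline value efficiently. Over assumed correlations of 0.2 to 0.7, the variance relative to baseline adjustment runs from 1.67 down to 1.18 for change and from 1.04 up to 1.96 for 24 months alone. These ratios assume equal variances at the two times, and the actual correlation is unknown. No bias in either comparison is shown, and the primary BDI-II analysis is unaffected.

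**What to change.** In Economic Analysis, replace the comparison at each time point and the analysis of change with one estimate: the 24-month between-arm difference in cost, adjusted for the participant's own baseline CSRI value. Use the same form for service use where it is a count or continuous. Inference should suit skewed data, for example a non-parametric bootstrap that respects practice clustering. This keeps the section's non-parametric intent and its commitment on clustering, and brings cost into line with Planned analyses. State that baseline costs will be described by arm without a test.

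The cost is wording and one model term. The baseline CSRI is already collected, so no new data or participants are needed.
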